## Abstract

**Purpose:**

Children with spastic cerebral palsy (CP) classified as Gross Motor Function Classification System (GMFCS) level IV face profound mobility limitations and are often excluded from intensive gait rehabilitation programs due to the severity of their impairments. Robotic-assisted gait training offers a promising avenue for functional improvement in this underserved population, yet empirical evidence remains scarce. This protocol describes a trial designed to evaluate the effects of a 6-month robotic gait training intervention on gross motor function, walking capacity, joint range of motion, muscle morphology, and psychological satisfaction in children with GMFCS level IV CP. Results will be reported in a subsequent publication following trial completion.

**Methods:**

This two-arm, parallel-group, randomized controlled trial will enroll 36 children aged 6–12 years with GMFCS level IV CP. Participants will be randomized 1:1 to either the intervention group (robotic gait training using the RoboCT Pediatric Lower Limb Rehabilitation Robot) or the control group (usual care as determined by family preference). The intervention group will receive 45-min sessions, three times per week for 24 weeks. Primary outcomes include Gross Motor Function Item Set and walking capacity (1-min walk test). Secondary outcomes include passive ankle joint range of motion, lower-limb muscle morphology via ultrasound, and psychological satisfaction. Linear mixed-effects models will evaluate group-by-time effects under an intention-to-treat framework.

**Discussion:**

This will be one of the first trials to explore long-term robotic gait training in children with GMFCS level IV CP. Findings may inform evidence-based rehabilitation approaches and improve access to technology-supported interventions in this highly underserved population.

**Clinical trial registration:**

ClinicalTrials.gov, NCT07049523.

## Introduction

1

Cerebral palsy (CP) remains the most common motor disability in childhood, affecting approximately 17 million people worldwide, with an estimated 2–3 per 1,000 live births (1, 2). In China alone, the number of children with CP is estimated to exceed 6 million, with approximately 40,000 new cases occurring each year (3). Notably, a substantial proportion of these children are classified as Gross Motor Function Classification System (GMFCS) levels IV or V, indicating they are either non-ambulatory or severely limited in voluntary movement (4). Children with GMFCS levels IV and V often exhibit pronounced spasticity, limited voluntary muscle control, and severe deficits in selective motor control. Muscle fibers in these children show altered histological features including reduced cross-sectional area, increased collagen deposition, and impaired oxidative capacity (5). These pathological characteristics further exacerbate limitations in force generation and movement efficiency. These children experience profound impairments in mobility, postural control, and independence, presenting critical challenges for their physical and psychological development.

As we recently reported in a systematic review (6), current physical rehabilitation strategies for children with CP are derived from studies involving ambulatory children (GMFCS I–III), while the severely affected population (GMFCS IV–V) remains underrepresented in the literature. The absence of walking ability in these children precludes participation in many conventional physiotherapeutic or strength-based programs, resulting in stagnated motor development and a cascade of secondary complications including muscle atrophy, contractures, and social exclusion (7). In addition to clinical burdens, non-ambulatory children with CP present significant lifelong economic challenges for families and healthcare systems. Estimates suggest that the lifetime cost of care for a single individual with CP can exceed $1.6 million USD in high-income countries (8), with costs related to direct medical care, assistive equipment, caregiving, and loss of productivity. In China, the economic burden is compounded by disparities in access to rehabilitation services and limited insurance coverage for long-term care.

Recent advancements in robotics and wearable technologies have opened new avenues for restoring movement in neurologically impaired individuals. Over the past 5 years, pediatric exoskeleton systems have progressed considerably, with improvements in adaptive joint actuation, trajectory control, and real-time feedback mechanisms that enhance both safety and engagement (9). Robotic exoskeletons and powered orthoses offer the potential to provide task-specific, repetitive, and intensive gait training while minimizing therapist workload (10). Such devices have shown promise in adult populations with spinal cord injury and stroke (11), and early-stage trials have extended these technologies to pediatric neuromuscular disorders, including CP (12). However, empirical data on the feasibility, safety, and efficacy of prolonged robotic gait training in children with GMFCS IV and V classifications are virtually nonexistent.

For children with GMFCS level IV, the clinical goal of robotic-assisted gait training is not to achieve independent ambulation, but to preserve and enhance residual motor capacity. By enabling structured, repetitive upright movement, exoskeleton training may help maintain joint range of motion, stimulate muscle morphology, mitigate secondary complications such as contractures, and foster postural stability. In addition, the experience of supported upright mobility could promote psychosocial benefits, including motivation, engagement, and perceived quality of life. These outcomes, while modest compared with independent walking, are meaningful for improving comfort, health, and participation in daily life.

This protocol outlines a prospective 6-month intervention trial aimed at evaluating the effectiveness of robotic exoskeleton gait training on motor and psychological outcomes in children with severe CP. Through this study, we aim to establish initial empirical evidence for the feasibility and potential benefits of exoskeleton-assisted rehabilitation in children who are traditionally excluded from active gait training. We hypothesize that children with GMFCS level IV CP will demonstrate measurable improvements in supported motor function, joint flexibility, and lower-limb muscle morphology, as well as greater psychological satisfaction and therapy engagement. These expected benefits, though not equivalent to achieving independent gait, represent clinically relevant improvements that can reduce secondary complications and enhance quality of life. This trial addresses a major gap in pediatric neurorehabilitation and may provide a critical foundation for scaling up robotic interventions in underserved clinical populations.

## Methods

2

### Study design

2.1

This study is a prospective, two-arm, parallel-group, randomized controlled trial designed to evaluate the effectiveness of robotic-assisted gait training in children with spastic cerebral palsy classified as GMFCS level IV. The study will be conducted in the College of Physical Education at the Hunan Normal University, community rehabilitation centers and affiliated hospitals across the city of Changsha, Hunan Province, China. The trial follows the recommendations of the SPIRIT 2025 statement for standardized trial protocol reporting (13). As shown in Figure 1, all participants undergo eligibility screening and baseline assessments prior to randomization (week 0). The intervention phase spans 24 weeks, with robotic gait training or usual care delivered continuously across this period. Outcome assessments are scheduled at three timepoints: baseline (week 0), midpoint (week 12), and post-intervention (week 24), except for ultrasound imaging, which is conducted only at baseline and post-intervention. This structured timeline ensures standardized evaluation across participants and facilitates monitoring of both short- and longer-term effects of the intervention.

**Figure 1 fig1:**
[figure not shown]
Schedule of enrolment, interventions, and assessments. GMFCS, Gross Motor Function Classification System; GMFM-IS, Gross Motor Function Measure – Item Set; PedsQL™ 3.0 NMM, Pediatric Quality of Life Inventory 3.0 Neuromuscular Module; ROM, range of motion.

Participant recruitment is expected to begin in October 2025, with the intended recruitment period lasting approximately 3 months. Under the original plan, all eligible participants will be enrolled during this initial window, allowing for synchronized intervention delivery and outcome assessments. The overall study duration, including intervention and follow-up assessments, is projected to span 8 months, concluding by December 2026. However, in anticipation of potential delays in reaching the full target sample size during the initial recruitment phase, a contingency plan has been established to allow for phased enrollment. If fewer than the required 36 participants are enrolled by the end of the first recruitment window, a second recruitment phase will be conducted beginning no later than March 2026, with the aim of completing final enrollment by June 2026. In this scenario, intervention and assessment timelines will be adjusted accordingly, with outcome evaluations staggered by cohort while maintaining the same study protocol and follow-up durations. This dual-path recruitment strategy is designed to maximize enrollment feasibility while preserving methodological integrity and adherence to the trial timeline.

### Trial status

2.2

This manuscript is based on Protocol Version 1.2, finalized in June 2025. At the time of manuscript submission, no participants have been enrolled. Recruitment is expected to begin in October 2025 and continue until June 2026, with the intervention and follow-up assessments scheduled through March 2027. The final report is expected to be published by June 2027.

### Participants

2.3

Eligible participants will be children aged between 6 and 12 years with a clinical diagnosis of spastic CP, confirmed by a licensed pediatric neurologist from the Xiangya Hospital, Central South University. Only children classified as level IV on the GMFCS will be included. These children must rely on assistive mobility devices, such as wheelchairs or posture support walkers, for activities of daily living prior to enrollment. All participants must be medically stable, able to sit upright for at least 30 min, and capable of following simple verbal or visual instructions with caregiver support.

Children classified as GMFCS level V will not be eligible for inclusion, based on pre-study consultation with the device manufacturer and experienced pediatric physical therapists, who jointly determined that the functional and cognitive demands of the robotic exoskeleton used in this study would likely exceed the safe participation threshold for this population.

Exclusion criteria include prior administration of botulinum toxin-A injections to the lower limb muscles within 6 months prior to baseline assessment; the presence of an intrathecal baclofen pump; or a history of lower limb orthopedic or neurosurgical interventions, such as tendon lengthening or selective dorsal rhizotomy, at any time prior to study participation. Additionally, children will be excluded if they present with uncontrolled epilepsy, severe cognitive impairment, or other comorbid conditions that, in the judgment of the study physician or intervention team, may interfere with safe use of the robotic device or adherence to the study protocol.

Written informed consent will be obtained from each participant’s legal guardian prior to enrollment. When appropriate, verbal or pictorial assent will also be sought from the child.

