### Randomization and blinding

2.5

Participants will be randomly assigned in a 1:1 ratio to either the intervention group (robotic gait training) or the control group (usual care) using a computer-generated randomization sequence. The allocation sequence will be generated using a random number generator in R (package randomizr version 1.0.0) to ensure allocation concealment. Block randomization with a fixed block size will be employed to maintain balance between the groups throughout the recruitment period.

The assignment will be managed by a researcher not involved in participant enrollment or outcome assessment. Group allocation will be revealed to participants and caregivers following enrollment due to the nature of the intervention, which precludes participant-level blinding. This trial will follow a single-blind design, in which the statistician performing the primary and secondary analyses will remain blinded to group allocation until all data collection and preliminary data checks are complete. All outcome assessors collecting GMFCS scores, gait parameters, ultrasound muscle measures, and psychological questionnaires will remain blinded to group allocation to minimize detection bias. In the event that unintentional unblinding occurs, this will be documented, and an independent statistician—who is not otherwise involved in the trial—will be invited to conduct additional sensitivity analyses to ensure the robustness of the findings.

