### Intervention

2.6

The intervention group will receive robotic-assisted gait training using the RoboCT Pediatric Lower Limb Rehabilitation Robot (RoboCT Limited Co., Hangzhou, China), a pediatric exoskeleton system designed for overground locomotor training. This device integrates real-time motion sensing, adaptive control algorithms, and customizable joint actuation to deliver precise and individualized gait training for children with minimal voluntary motor control. The system includes powered actuators at the hip, knee, and ankle joints, a dynamic body-weight support harness, and multi-axis load and torque sensors for continuous monitoring of movement safety. Trajectory control is achieved through programmable gait cycles, allowing therapists to adjust joint angles, step length, and walking speed according to each child’s tolerance and progression. The device employs closed-loop feedback to ensure smooth movement execution and adaptive support. Safety features include automatic shutdown in response to excessive joint torque, misalignment detection, and redundant harness support. These integrated mechanical and control features ensure that the system can safely deliver task-specific, repetitive gait training in a pediatric population.

Robotic sessions will be conducted three times per week over a period of 24 weeks, with each session lasting approximately 45 min. All sessions will be conducted at a designated training site under the supervision of certified pediatric rehabilitation therapists. Each robotic training session will follow a structured protocol comprising several core components designed to promote safe, progressive, and task-specific gait rehabilitation. Sessions will begin with a brief warm-up period, which includes passive joint mobilization and postural alignment to prepare the child for exoskeletal engagement. Following this, participants will engage in assisted overground walking guided by the device’s programmable gait cycle, which delivers coordinated joint movements to simulate a physiological walking pattern.

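### The intervention team, which sees the open treatment, may itself exclude children on judgment, so under fixed blocks a guess at the next arm could influence who is enrolled

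*Protocol article*

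**What the plan says.** **Who may exclude (Protocol article, 2.3).** Besides the listed criteria, a child is excluded for any further comorbidity that, "in the judgment of the study physician or intervention team, may interfere with safe use of the robotic device"; a threat to adherence is the second ground. The conditions are not listed, and the word joining the two deciders lets the intervention team act without the physician.

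**How arms are assigned (2.5).** "Block randomization with a fixed block size will be employed to maintain balance between the groups throughout the recruitment period". The block size is not given. "Group allocation will be revealed to participants and caregivers following enrollment due to the nature of the intervention".

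**What is kept apart (2.5).** "The assignment will be managed by a researcher not involved in participant enrollment or outcome assessment". Outcome assessors and the statistician are blinded. Nothing separates the intervention team from eligibility decisions. The section credits the random number generator with concealing allocation, but producing a sequence does not conceal it.

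**Who sees the robot arm (2.6).** All sessions take place at a designated site "under the supervision of certified pediatric rehabilitation therapists".

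**Timing (2.1, 2.2).** Each child is screened and assessed at baseline before being randomized. The original plan is a window of about 3 months with synchronized delivery, and a second recruitment phase with staggered cohorts is the contingency. Section 2.2 is broader: "Recruitment is expected to begin in October 2025 and continue until June 2026".

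**The concern.** Discretionary exclusion before randomization is ordinary and harmless as long as whoever uses it cannot foresee the next arm. Here the group that holds the discretion also treats one arm openly, and a balanced blocked sequence carries information about what comes next.

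The demands on the arms are unequal. A robot child must complete three sessions a week for 24 weeks, while a control child continues usual care. A comorbidity thought to threaten adherence therefore weighs more when the robot seems due than when control does. If that view affected even a few borderline decisions among 36 children, the arms could differ in capacity to improve. Intention-to-treat analysis would not undo this, because the steering happens before randomization.

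**Working it through.** **1. The plan's own figure.** The article gives no figure on predictability. Its target of 36 is the only input needed, and it reproduces. A two-sided t-test with d = 1.0, alpha 0.05 and power 0.80 needs 16.71, so 17 per arm (power 0.807) and 34 in total; 34 / 0.95 = 35.8, so 36. This point does not change it.

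**2. Can screening overlap with training?** Training lasts 24 weeks. Thirty-six children in about 13 weeks is 36 / 13 = 2.8 a week; from October to June (about 39 weeks) it is 36 / 39 = 0.9 a week. Either window allows later screening to run alongside earlier training, unless all starts are held until enrollment closes. The faster rate makes it likelier that several children are between screening and disclosure at once.

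**3. How good is the guess?** Rule: guess the arm with fewer children so far, and toss a coin at a tie. Assumed: 1:1 blocks of 4, with every earlier arm in both groups known.

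- Position 1: 1/2.
- Position 2: 2/3 (two of the three remaining places belong to the other arm).
- Position 3: the first two match with probability 1/3 (next arm certain) and differ with probability 2/3 (coin toss), so 1/3 × 1 + 2/3 × 1/2 = 2/3.
- Position 4: 1.
- Mean: (1/2 + 2/3 + 2/3 + 1) / 4 = 0.708, or 25.5 of 36.

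The same rule when the most recent arms are not yet known:

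| Earlier arms unknown | Positions 1 to 4 | Mean | Expected correct of 36 |
|---|---|---|---|
| 0 | 1/2, 2/3, 2/3, 1 | 0.708 | 25.5 |
| 1 | 1/2, 1/2, 2/3, 2/3 | 0.583 | 21 |
| 2 | 1/2, 1/2, 1/2, 2/3 | 0.542 | 19.5 |
| 3 | 1/2 throughout | 0.500 | 18 |

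**4. Other block sizes, all earlier arms known.**

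| Fixed block size (assumed) | Correct guess | Certain of 36, if block size is known |
|---|---|---|
| 2 | 75% | 18 |
| 4 | 71% | 12 |
| 6 | 68% | 9 |
| 12 | 64% | about 5 |

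**5. Does varying the block size close the route?** Not alone. In simulation the same rule was right for 70% (sizes 2/4/6), 69% (4/6) and 68% (4/6/8) with all earlier arms known. For 4/6/8 it was right for 59%, 56% and 53% with one, two and three arms unknown. Undisclosed, varied sizes mainly remove the certainty that comes from knowing the block size; the running-count guess survives.

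**6. From guess to bias.** Suppose the mean prognosis of admitted children moves by +η SD when robot is guessed, −η when control is guessed, and 0 at a tie. With guess rate g the spurious difference between arms is 2η(2g − 1). For blocks of 4 and an assumed η = 0.25:

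- all earlier arms known: 2 × 0.25 × (2 × 0.708 − 1) = 0.21 SD;
- one unknown: 2 × 0.25 × (2 × 0.583 − 1) = 0.08 SD;
- three unknown: 0.

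The documents give no basis for η, so this shows how the quantities connect and is not an estimate.

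**The case against.** **The criterion is narrower than free choice.** A reader might infer that the team may turn away any child who looks hard to train. The text does not say that: a comorbid condition is required, and the diagnosis, GMFCS level, sitting tolerance and ability to follow instructions are fixed separately. This stands. The discretion covers borderline comorbidity, not general promise.

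**The team's knowledge is partly inferred.** Delivering the treatment shows who received the robot. The guess needs both arms' counts, and no section says the team learns who went to control, or when. It could work this out if it also takes part in eligibility decisions, but that is inference. This stands as a condition on the point.

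**The 71% is a ceiling.** It assumes immediate, complete knowledge. One pending child brings it to 58% and three bring it to chance. If synchronized delivery means that nobody's arm is revealed until all are enrolled, the route is closed. The article permits that reading but does not state it, and the second cohort and longer window point the other way.

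**The analysis looks at change.** Under the group-by-time model in 2.8, a difference in baseline level alone does not bias the contrast; a difference in trajectory would. This narrows the harm without removing it.

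**Operational detail may sit in the full protocol.** That is fair for sign-off forms and screening logs, and their absence is not held against the article. The article does, however, state who may exclude, and names the intervention team. The team's case-by-case safety view also has real value, so the remedy should not silence it.

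**Conclusion.** The point holds as a conditional risk. A team that treats the robot arm openly has its own discretion over eligibility, allocation is in fixed blocks, and the stated separation does not cover that team. The route depends on three things: later children being screened after earlier arms are known, the team knowing both running counts, and the blocking in 2.5. With blocks of 4 (assumed) the guess is right at most about 71% of the time, about 58% with one arm pending, and near 50% with several pending or with disclosure held until enrollment closes.

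A reader might go further and conclude that the trial will be biased in favor of the robot, or that seven guesses in ten will succeed. The documents support neither. They do not give the block size, the delay between screening and disclosure, or how often the discretion would be used, so the effect on the result cannot be estimated. The change is worth making because it is cheap and, when the article was submitted, no child had been enrolled.

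**What to change.** **In 2.3:** state that the study physician, without access to earlier allocations, makes the final eligibility decision and records it before the allocation is requested. The intervention team contributes a documented device-safety opinion, also given before allocation, but does not itself decide exclusion on expected adherence.

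**In 2.5:** replace the fixed block size with randomly varied sizes that are not disclosed to staff who enroll or treat. The two changes belong together. Varied blocks alone leave a running-count guess at 68% to 70% when all earlier arms are known; taking the decision from people who know the counts is what closes the route.

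**Cost:** about a sentence in each section. The small downside is that the device team advises rather than decides, so its opinion must reach the physician before allocation. The safety criteria, sample size and analysis are unchanged.
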